### Other Planned Exploratory Analyses

To evaluate the effect of fish oil supplementation on omega-3 fatty acid concentrations in maternal blood, we will use a mixed effect model for longitudinal data because the omega-3 fatty acid concentrations will be measured twice for each participant (at baseline and at 34-36 weeks gestation). Using this model, we can assess both the time averaged difference in the concentration between the three groups as well as the change in the concentration over the two measurement times between the three groups. To evaluate the effect of fish oil supplementation on the proinflammatory cytokines referenced, we will use a mixed effect model for longitudinal data because each proinflammatory cytokine level will be measured twice for each participant (at baseline and at 34-36 weeks gestation). Using this model, we can assess both the time averaged difference in the levels between the three groups as well as the change in concentration over the two measurement times between the three groups. To evaluate the effect of fish oil supplementation on standard obstetrical outcomes including but not limited to length of gestation, birth weight, Apgar score, mode of delivery, blood loss at delivery, and preeclampsia, we will use multiple regression for continuous outcomes variables and logistic regression for dichotomous outcome variables, and in either of these approaches, an indicator for fish oil supplementation will be the primary independent variable.

The exploratory aims are intended to generate preliminary data elucidating the possible mechanism of action of fish oil supplementation in the prevention of depression in pregnancy and the postpartum period. In particular, the role of fish oil in inhibiting production of proinflammatory cytokines may provide an explanation for the observed link between depression in pregnancy and preterm birth, a condition known to be associated with inflammation. Although we will be unable to definitively explore these relationships in the proposed study, we intend for these aspects of the study design to generate preliminary data which will allow us to refine our dosing, expected effect sizes, and hypotheses for a larger, multicenter study of the effectiveness of fish oil in prevention of major depression in pregnancy and postpartum.

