### Study Visits

As much as possible, the four study visits will be coordinated with the subjects' routine prenatal care or ultrasound appointments. Visit #1 will occur between 12 and 20 weeks' gestation. Full written informed consent will be obtained. Baseline demographic and past medical and obstetrical history data will be collected. The baseline BDI (Beck Depression Inventory) will be administered. After a 3-hour fast, subjects will have their blood drawn to measure their baseline omega-3 fatty acid and proinflammatory cytokine levels (IL-1β, IL-6, and TNF-α). Subjects will be given a 3 month supply of the study supplement at this visit. Subjects will be instructed to take three capsules twice daily with meals and to return all unused capsules to the research team at their next study visit.

The second study visit will take place between 26 and 28 weeks gestation. During this visit, the BDI will be completed and the MINI will be re-administered to assess for MDD, suicidal ideation and psychiatric co-morbidity. The subjects will return their prescriptions to the study staff and all unused capsules will be counted. A two month supply of the study supplement will be given to each subject.

The third study visit will take place between 34 and 36 weeks gestation. During this morning visit, the BDI will be completed and the MINI will be re-administered. In addition, a second fasting blood sample will be obtained to measure the participant's omega-3 fatty acid levels and proinflammatory cytokine levels (IL-1β, IL-6, and TNF-α). At this visit, a three-month supply will be dispensed in order to provide women with sufficient doses until the postpartum visit. Each participant will be provided with a packet containing sterile tubes for collection of cord blood. Participants will be instructed to bring this packet with them to the hospital when they present to the Labor and Delivery unit.

When the subject presents for delivery, clinical staff will be notified that the patient is a study participant. After delivery of the baby, cord blood will be collected and proinflammatory cytokine levels and fatty acid levels will be assayed (visit #4).

The final study visit will take place at the participant's 6 week postpartum check-up. During this visit, the BDI will be completed and the MINI will be re-administered. Participants will receive $20 and a parking voucher for each study visit that they attend.

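### The time-averaged biomarker difference mixes a pre-treatment sample with the only on-treatment sample, so it estimates half the supplement effect and should not stand beside change as an effect measure

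*Protocol article*

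**What the plan says.** Under Other Planned Exploratory Analyses, the protocol article sets out a longitudinal mixed model for fatty acids and repeats it for cytokines. The sampling is explicit: for cytokines, "each proinflammatory cytokine level will be measured twice for each participant (at baseline and at 34-36 weeks gestation", and the fatty acid schedule is the same.

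Two contrasts are then named for judging the supplement. For fatty acids the first is "the time averaged difference in the concentration between the three groups"; for cytokines it is "the time averaged difference in the levels between the three groups". The second, in the cytokine wording, follows directly: "as well as the change in concentration over the two measurement times between the three groups". The text does not say which of the two is the effect estimate.

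Study Visits fixes the timing of the first sample. At visit 1, "subjects will have their blood drawn to measure their baseline omega-3 fatty acid and proinflammatory cytokine levels". Supplement is first dispensed at that same visit: "Subjects will be given a 3 month supply of the study supplement at this visit".

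Secondary Outcomes, items c and d, describe the biomarker outcomes as changes in fatty acid concentrations and in cytokine levels across these two time points.

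**The concern.** Averaging over time makes sense when several measurements are taken on treatment and each carries the effect. Here only one of the two does. The other precedes the first capsule, so any difference between arms in it is chance. Averaging the two dilutes the effect and adds baseline noise.

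These analyses serve the first two secondary aims: the relation of the supplements to plasma fatty acids and symptoms, and the cytokine mechanism. The article says the exploratory work should help shape a larger trial, including its expected effect sizes. With two contrasts of equal standing, one could be near null while the other is clear, and the section gives no rule for which to read as the effect.

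**Working it through.** **Inputs from the protocol.** There are two samples per woman, at baseline and at 34-36 weeks. The first is drawn at the visit where supplement is first given out. There are three randomised arms.

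**Inputs not in the protocol, so assumed.** The true 34-36 week difference D, a common standard deviation s at both visits, and the within-woman correlation r between the two samples, taken as 0.3, 0.5 and 0.7.

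**The plan's own figure.** None is given for the biomarkers. The only sample-size calculation is for the Beck Depression Inventory: group means 8.4, 4.2 and 4.2, SD 6.4, 35 per group. It reproduces (variance of means 3.920, effect size 0.0957, power 0.805), but it has no bearing here beyond supplying a group size.

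**Step 1: what each contrast estimates.** The expected difference between arms is 0 at baseline and D at 34-36 weeks.
- Time average: (0 + D)/2 = D/2.
- Change: D − 0 = D.
- 34-36 week difference adjusted for baseline: D.

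A simulation of 2,000 trials with 35 per group and a true difference of 1.00 SD gave means of 0.505 for the time average and 0.996 for change.

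**Step 2: per-woman variance.**
- Time average: s²(1 + r)/2.
- Change: 2s²(1 − r).
- Baseline-adjusted: s²(1 − r²).

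**Step 3: efficiency relative to the baseline-adjusted comparison** (ratio of squared effect to variance).
- Time average: [(D²/4) / (s²(1 + r)/2)] ÷ [D² / (s²(1 − r²))] = (1 − r)/2.
- Change: [D² / (2s²(1 − r))] ÷ [D² / (s²(1 − r²))] = (1 + r)/2.

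**Step 4: power when the baseline-adjusted comparison has 80%.** For a two-sided 5% normal test, 80% power needs a standardised effect of 1.96 + 0.84 = 2.80. Multiply this by the square root of the relative efficiency, subtract 1.96 and read off the normal probability.

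| r (assumed) | Time average: efficiency | Time average: power | Change: efficiency | Change: power |
|---|---|---|---|---|
| 0.3 | 35% | 38% | 65% | 62% |
| 0.5 | 25% | 29% | 75% | 68% |
| 0.7 | 15% | 19% | 85% | 73% |

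For r = 0.5, the time average gives 2.80 × √0.25 = 1.40, and Φ(1.40 − 1.96) = 0.29. Change gives 2.80 × √0.75 = 2.43, and Φ(2.43 − 1.96) = 0.68.

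**Step 5: an absolute example.** Take D = 0.6 SD and r = 0.5 (both assumed), with 35 per group.
- Time average: SE = √(2/35 × 0.75) = 0.207; 0.30/0.207 = 1.45; power 30%.
- Change: SE = √(2/35 × 1.00) = 0.239; 0.60/0.239 = 2.51; power 71%.
- Baseline-adjusted: SE = √(2/35 × 0.75) = 0.207; 0.60/0.207 = 2.90; power 83%.

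At this correlation the time average and the adjusted comparison have the same standard error. The whole loss comes from halving the effect.

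**The case against.** The strongest reply is that the right contrast is already in the plan. The same sentences that name the time average also name the change contrast, which estimates the full D, and Secondary Outcomes defines these outcomes as changes. The wording says what the model can assess; it does not single out the time average as the effect estimate. This stands, and it limits the point to one of two listed contrasts.

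A reader might go further and infer that a halved effect will be carried into the design of the larger trial, or that a real fatty acid or cytokine effect will be declared absent. The document supports neither. It speaks of expected effect sizes in general and does not say that the time-averaged figure would supply them. A real effect would be missed on this ground only if the time-averaged test decided alone, which nothing states.

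It is also fair to say that preferring baseline adjustment to change is a gain in efficiency, since change is unbiased. The power figures depend on assumed correlations and on an 80% benchmark chosen for comparison. Finally, the article itself describes this work as preliminary and not definitive.

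What remains is that the plan offers, as a measure of the supplement effect, a contrast that does not estimate that effect. This is a stated choice of contrast, not a detail left for an analysis plan.

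**Conclusion.** The point holds for the time-averaged contrast, and only for it. With equal weights its expectation is half the 34-36 week difference, whatever the true effect and the correlation. Its power is about 19% to 38% where a baseline-adjusted comparison has 80%, for assumed correlations of 0.7 down to 0.3 and equal variances at the two visits.

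The factor of one half rests on equal weighting. That is the natural reading of a model that also carries the group-by-time term needed for the change contrast. If the model were fitted without that term and the on-treatment SD were larger, the weight on the 34-36 week sample would fall: with an SD ratio of 1.5 and a correlation of 0.3 it is 0.23. One half is therefore not the worst case.

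The supplement effect is not lost from the plan as a whole, because the change contrast recovers it. The analyses are exploratory, and the primary outcome and its sample size are untouched. This is an inexpensive correction to a secondary part of the plan.

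**What to change.** In Other Planned Exploratory Analyses, remove the time-averaged difference as an effect measure for fatty acids and for cytokines. Name the difference between arms at 34-36 weeks, adjusted for the baseline value, as the effect estimate. It can come from ANCOVA or from the planned mixed model with arm means constrained to be equal at baseline. The constrained model also keeps women who have only one of the two samples. Change from baseline may still be reported as the description matching Secondary Outcomes.

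The cost is two sentences, one for each biomarker class. No new sample, visit or software is needed. The adjusted comparison is at least as precise as change, because (1 + r)/2 never exceeds 1.

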### Sample Size Considerations

We hypothesize that (i) fish oil supplementation will reduce the severity of depressive symptoms in the postpartum period among women at risk and that the (ii) EPA-rich fish oil (intervention #1) and DHA-rich fish oil (intervention #2) will be equally efficacious in reducing depressive symptoms. Our sample size calculation is based on the premise that fish oil supplementation of either the EPA-rich or DHA-rich dose will result in a 50 percent reduction in the mean BDI score at 6 weeks postpartum. Sample size calculations were generated in *nQuery Advisor *Version 6.01 based on data from a previous study conducted among the target population by one of the co-investigators, [name]. In that observational study, she observed a mean BDI score of 8.4 with a standard deviation of 6.4 among postpartum mothers at risk for depression. Assuming a significance level of 0.05, a one-way analysis of variance test, a variance of means (variance of the individual group means) of 3.920, a standard deviation of 6.4, and an effect size (the index of the separation expected among the observed means) of 0.0957, we will need to recruit 105 pregnant women (35 pregnant women in each of the three groups) to have 80% power to detect at least one group difference in the mean BDI score. We propose to recruit 126 pregnant women to account for the possibility of up to 10% study dropout and 10% initiating antidepressant therapy during the study period (to provide sufficient numbers for subgroup analyses).

Our decision to hypothesize a 50% reduction in the mean BDI score between intervention and control groups is based on results from published studies. Freeman and colleagues recently conducted two clinical trials[41,42] of omega-3 fatty acid supplementation and perinatal depression, using the EPDS as their primary measure of depressive symptomatology and reported a 51% and 41% reduction in EPDS score over an 8 week study period. A comparable study in a non-pregnant population demonstrated a similar effect size[43].

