### Descriptive Analyses

Once data have been collected, descriptive statistics (means, standard deviations, frequencies, proportions, and graphical displays) will be computed for all study variables. The distributions of outcome variables will be assessed to determine if distributional assumptions are valid. Decisions will be made at this time about the creation of category boundaries for certain continuous covariates, using well-established cut-points where appropriate. All analyses will be done on an intent-to-treat basis. Baseline analyses will be performed to determine if the three study groups are comparable or not with respect to various variables including age, parity, and body weight. If any of the baseline variables are shown to be different across the three groups, any outcome comparisons across the three groups will be adjusted for the potential confounding effect of these variables. In all analyses, we plan to control for possible confounders, and covariates that change the coefficient of interest by more than 10% will be retained in the final multivariable model.

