## Discussion

The proposed study will assess the effect of two fish oil supplements on depressive symptomatology in an at-risk population through a randomized controlled design. Strengths to this study include its double-blind, placebo-controlled design and its inclusion of two intervention groups to test both an EPA-rich and a DHA-rich supplement. To our knowledge, the proposed study is the first to directly compare these two fish oils in a pregnant population. Results of previous systematic reviews indicate that differences in fish oil composition may account for the heterogeneity of the observed results of prevention and treatment trials for depression[29,30]. However, this hypothesis has not been previously tested in a RCT comparing both interventions.

The proposed study has the potential to impact clinical care for pregnant women at risk for depression during and after pregnancy. There is a significant burden of disease associated with major depression, and although depression during and following pregnancy occurs at a frequency similar to preeclampsia (5-8%) and preterm birth (11%), it receives much less clinical attention. The disability associated with depression is as great as the disability of other chronic diseases such as hypertension, diabetes, and rheumatoid arthritis[44]. Maternal depression during pregnancy may also constitute a risk factor for suboptimal neurobehavioral development of the child. Dietary supplementation with molecularly distilled omega-3 fatty acid preparations may provide a safe and well-tolerated means for pregnant women to reduce their risk for depression.

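### Preeclampsia would yield only about 6-10 events, too few for logistic regression with covariates kept by a 10% change rule

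*Protocol article*

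**What the plan says.** Protocol article, Other Planned Exploratory Analyses: the obstetric outcomes listed include mode of delivery and preeclampsia alongside naturally continuous ones such as birth weight and length of gestation. For these, "we will use multiple regression for continuous outcomes variables and logistic regression for dichotomous outcome variables". The main explanatory variable is one indicator for fish oil, which read literally pools the two active arms against placebo. The same section presents these analyses as exploratory and concedes that they cannot settle the relationships studied.

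Descriptive Analyses: "In all analyses, we plan to control for possible confounders". Covariates that shift the coefficient of interest by more than 10% stay in the final model, and variables found to differ between groups at baseline are also adjusted for. The number of candidate covariates is not fixed.

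Sample Size Considerations: "We propose to recruit 126 pregnant women to account for the possibility of up to 10% study dropout and 10% initiating antidepressant therapy".

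Discussion: the only event rates in the article are background remarks, 5-8% for preeclampsia and 11% for preterm birth. No expected event count is given for any obstetric outcome.

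**The concern.** Each piece is ordinary taken alone. Together, for preeclampsia, they put a multivariable logistic model with data-driven covariate retention on a handful of events.

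Two things go wrong. If either treatment group has no case, maximum likelihood has no finite odds ratio. And when the treatment coefficient is near zero or poorly estimated, a 10% relative change is easy to reach by chance, so the retention rule tends to admit covariates that are pure noise. With so few events, the extra terms can push the estimate further from the truth.

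At stake is whether the preeclampsia result can be read at all: a missing, infinite or badly exaggerated odds ratio in place of a simple comparison of counts. The primary depression outcome is not affected.

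**Working it through.** **The plan's own figure.** The article gives no event count to reproduce, so the check starts from its sample size. A 50% reduction in both active arms gives means of 8.4, 4.2 and 4.2, with overall mean 5.6. The variance of means is (2.8² + 1.4² + 1.4²)/3 = 3.92, and 3.92/6.4² = 0.0957. Both match the article. Power from the noncentral F distribution is 0.805 at 35 per group and 0.793 at 34, so 35 per group (105) is right, and 105 × 1.2 = 126. Equal arms of 42 are assumed below.

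**Expected events (N × rate).**
- Preeclampsia: 126 × 0.05 = 6.3; 126 × 0.08 = 10.1. In the placebo arm: 42 × 0.05 = 2.1 to 42 × 0.08 = 3.4.
- After 10% dropout (113 women): 5.7 to 9.0.
- Preterm birth: 126 × 0.11 = 13.9.

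**Chance that a group has no event** (one fish-oil indicator, no true effect). With event rate p, this is 1 − [1 − (1−p)^42] × [1 − (1−p)^84].

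| p | (1−p)^42 | (1−p)^84 | Either group empty |
|---|---|---|---|
| 5% | 0.116 | 0.013 | 12.8% |
| 6.5% | 0.059 | 0.004 | 6.3% |
| 8% | 0.030 | 0.001 | 3.1% |
| 11% | 0.0075 | 0.0001 | 0.8% |

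At 38 per arm, the first three results become 16.0%, 8.3% and 4.4%.

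**How far the odds ratio misses.** Simulation of 84 against 42. The table gives the share of trials in which the odds ratio is non-finite or off by more than threefold. The number and strength of covariates are assumed.

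| Setting | Rate | Maximum likelihood | Firth |
|---|---|---|---|
| True OR 1, no covariates | 5% | 28.0% | 16.8% |
| | 8% | 19.3% | 13.7% |
| True OR 1, three covariates (log OR 0.4 each) | 5% | 33.7% | 21.7% |
| | 8% | 20.0% | 13.7% |
| True OR 1, four unrelated covariates | 5% | 33% | 23% |
| | 6.5% | 24% | 15% |
| | 8% | 21% | 13% |
| True OR 0.5, three covariates | 5% | 42.5% | 26.0% |
| | 8% | 27.0% | 17.3% |

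Runs: 1,500 per setting, except the four-covariate rows (2,000 maximum likelihood fits, 600 Firth fits). The rows with a true odds ratio of 0.5 show that Firth's gain is not merely shrinkage towards a true null.

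**The 10% rule applied as written** (eight candidate covariates, all noise; number assumed; no true effect). Among trials with events in both groups, about three of the eight were retained on average, and at least one in 86-89% of trials. Compared with the unadjusted fit, the share non-finite or off by more than threefold rose from 28% to 36% at a 5% rate, from 23% to 27% at 6.5%, and from 18% to 21% at 8%. A second run of the same design gave 34%, 24% and 22% under the rule, against about 18-19%, 13-14% and 13% with Firth.

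**Splitting the excess.** At a 5% rate with no true effect, going from three covariates to none lowers the maximum likelihood share from 33.7% to 28.0%; Firth without covariates lowers it further to 16.8%. At 8% the steps are 20.0%, 19.3% and 13.7%. What remains after both steps comes from the small number of events.

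**The case against.** The strongest objection is that the article says only logistic regression. It does not say maximum likelihood, and Firth-penalised and exact fits are logistic regression too. The choice of estimator for a rare exploratory outcome is often left to an analysis plan, which is not shown. That stands as far as the estimator goes. It does not cover the retention rule, which the article states outright for all analyses and which makes matters worse at these counts whichever plan follows.

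It is also fair that much of the error is sampling error, that the 5-8% is a background figure, and that the article defines preeclampsia by its own blood-pressure rise plus proteinuria, so the trial's count could differ.

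Three stronger readings are tempting, and the document does not support them:
- A reader might infer that the dichotomous obstetric outcomes as a group have this problem. The 6-10 count is for preeclampsia alone. Preterm birth at 11% gives about 14 events and under 1% empty groups under no effect, and no rate is given for mode of delivery.
- A reader might compute the chance that any of three arms is empty: 31% at a 5% rate, 17% at 6.5%, 9% at 8%. That suits a model with separate EPA and DHA terms. The section names one fish-oil indicator, for which the figures are 13%, 6% and 3%.
- A reader might infer that these odds ratios would set the effect size of the larger study. The article describes that study as one of preventing major depression; nothing says a preeclampsia odds ratio would size it.

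**Conclusion.** The point holds as a minor one, for preeclampsia and any binary obstetric or neonatal outcome with similarly few events. At the article's 5-8% rate, about 6-10 events are expected among 126 women. With the pooled indicator and no true effect, maximum likelihood gives no finite estimate in about 13% of trials at 5%, 6% at 6.5% and 3% at 8%. With covariates, roughly 20-35% of trials give an odds ratio that is non-finite or off by more than threefold, against roughly 13-23% with Firth. A better method therefore buys a reduction of about 6 to 15 percentage points; it does not make the estimate precise.

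This rests on equal arms of 42, the background rate applying to this trial, the covariate numbers and strengths assumed above, and maximum likelihood as the usual meaning of an unqualified logistic regression. The analysis is exploratory and no primary conclusion depends on it.

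**What to change.** In Other Planned Exploratory Analyses, add that for preeclampsia, and for other dichotomous obstetric or neonatal outcomes with similarly few events:
- counts by arm and risk differences versus placebo will be reported with exact or score intervals;
- the 10% change-in-coefficient rule will not be applied;
- any odds ratio will come from Firth-penalised or exact logistic regression.

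Name the outcomes covered, or the event count below which this applies, before unblinding; the documents do not dictate a particular threshold. The regression plan can stay for the other outcomes.

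Cost: a sentence or two of text, a little extra analysis work, and no multi-covariate adjustment for rare outcomes. The article fixes SAS 9.1, so confirm that this version offers the chosen method.

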## Methods

### Aims

The aim of this study is to determine whether EPA or DHA will prevent pregnancy-related depressive symptoms. We hypothesize that EPA-rich fish oil supplementation and DHA-rich fish oil supplementation will reduce the risk of antenatal and postpartum depressive symptoms in women who are at elevated risk for depression based on a previous history of major depressive disorder, a previous history of postpartum depression, or an Edinburgh Postnatal Depression Scale (EPDS) score between 9 and 19 in early pregnancy. The study will also directly compare the effects of EPA and DHA on depressive symptoms as measured by the Beck Depression Inventory score. In addition we hypothesize that fewer pregnant women assigned to the fish oil supplementation will require treatment with antidepressant medications and if medicated, a lower total dose will be required than for women receiving placebo. We will recruit pregnant women who are between 12-20 weeks gestation and will follow them through their pregnancies and up to 6 weeks postpartum. The women participating in this study will be receiving prenatal care at two health systems in southeastern Michigan, the University of Michigan Hospitals and Clinics and St. Joseph Mercy Health System/Integrated Health Associates. These health systems are located in Ann Arbor, Michigan and Ypsilanti, Michigan and the surrounding communities.

This study also has three secondary aims that will generate preliminary data on possible mechanisms of action of EPA and DHA in mental health. First, we will examine the relationship between EPA and DHA, maternal plasma fatty acid levels, and symptoms of depression. Second, we will explore whether EPA and DHA reduce depressive symptoms by reducing synthesis of pro-inflammatory cytokines IL-6, IL-1β, and TNF-α. Third, we will examine the relationship between EPA and DHA and standard pregnancy outcomes, including birth weight and length of gestation.

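### The obstetric-outcome models carry a single fish-oil term, which read literally pools the EPA-rich and DHA-rich arms and does not fit the aim they serve

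*Protocol article*

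**What the plan says.** All references are to the Protocol article.

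- **Aims.** The third secondary aim reads: "Third, we will examine the relationship between EPA and DHA and standard pregnancy outcomes, including birth weight and length of gestation". The secondary aims as a set are introduced as preliminary: "This study also has three secondary aims that will generate preliminary data on possible mechanisms of action of EPA and DHA in mental health". A head-to-head comparison of the oils is promised for depressive symptoms: "The study will also directly compare the effects of EPA and DHA on depressive symptoms as measured by the Beck Depression Inventory score".
- **Other Planned Exploratory Analyses, obstetric outcomes.** Continuous outcomes get multiple regression and binary ones get "logistic regression for dichotomous outcome variables". In both, "an indicator for fish oil supplementation will be the primary independent variable".
- **Same section, fatty acids and cytokines.** These models compare all three arms; for the cytokines, the target includes "the change in concentration over the two measurement times between the three groups".
- **Multivariable Analyses.** The between-subject factor in the BDI model is the supplement group.
- **Discussion.** Among the strengths listed is "its inclusion of two intervention groups to test both an EPA-rich and a DHA-rich supplement".

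**The concern.** In a regression, one indicator is one 0/1 column and yields one coefficient. With two active arms and a placebo arm, a fish-oil indicator estimates the combined active arms minus placebo. The two oils' effects cannot be recovered from that coefficient.

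The aim behind these models names EPA and DHA, and the models beside them keep the arms apart. The hypothesis of equal efficacy under Sample Size Considerations is confined to depressive symptoms. Nothing in the article extends it to gestation, birth weight, blood loss or preeclampsia.

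At stake is how well the obstetric results can be interpreted. An effect of one oil would be diluted by the other arm, and opposite effects would offset each other. This includes blood loss at delivery, where a difference between oils would be relevant to safety. The section also says that the exploratory results are meant to inform effect sizes and hypotheses for a larger trial, and a pooled coefficient supplies no oil-specific obstetric effect size for that.

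**Working it through.** **1. The plan's own figures.** The article gives no figure for the obstetric models. Its only calculation is for the BDI, and it reproduces:

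- Means of 8.4, 4.2 and 4.2 have a grand mean of 5.6. The variance of means is (2.8² + 1.4² + 1.4²)/3 = 11.76/3 = 3.920.
- Effect size = 3.920/6.4² = 0.0957.
- The non-central F distribution with three groups and alpha 0.05 gives 80.5% power at 35 per group (79.3% at 34).

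So 105 women, 35 per group, is confirmed. None of this bears on the obstetric term.

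**2. The treatment term, model by model.**

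| Outcome | Treatment term as written | Separates the oils? |
|---|---|---|
| BDI | supplement group as a factor | yes |
| Fatty acids | three groups | yes |
| Cytokines | three groups | yes |
| Obstetric outcomes | one fish-oil indicator | no, read literally |

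**3. What a pooled term costs or saves.** Assumptions: equal arms of 126/3 = 42, no losses, a continuous outcome with common SD (results in SD units), no covariates, normal approximation. For logistic models the results are only approximate.

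- SE of the pooled contrast = √(1/84 + 1/42) = 0.189.
- SE of one oil versus placebo = √(1/42 + 1/42) = 0.218.
- Ratio = 0.218/0.189 = 1.155, so separate contrasts have a standard error about 15% larger. The ratio is the same for any equal arm size.
- Difference detectable with 80% power: 0.53 SD pooled, 0.61 SD for one oil. At 35 per arm: 0.58 and 0.67 SD.

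**4. Illustration: only one oil acts.** With effect d in one arm and none in the other, the pooled coefficient is (d + 0)/2 = d/2.

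- Ratio of z statistics, pooled to direct = 0.5 × 1.155 = 0.577.
- If the direct contrast has 80% power, its expected z is 1.96 + 0.84 = 2.80. The pooled z is 0.577 × 2.80 = 1.62, and power = P(Z > 1.96 − 1.62) ≈ 0.37.
- With d set at 0.5 SD (an assumed value), power is 26% pooled and 63% direct.

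**5. The other scenarios.** With +0.5 SD in one arm and −0.5 SD in the other, the pooled coefficient is 0. With 0.5 SD in both arms, the pooled term has 75% power against 63% for each separate contrast, so pooling does better.

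**The case against.** **The wording may be loose.** The article never says that the arms are combined for obstetric outcomes. It uses fish oil supplementation as shorthand for the whole three-arm intervention, including in the sentences that open the fatty-acid and cytokine analyses. Descriptive Analyses also has a general rule on adjusting outcome comparisons across the three groups and does not exempt obstetric outcomes. This stands in part: pooling is an inference. But the two neighbouring models begin with the same shorthand and go on to specify three groups, whereas the obstetric sentence goes on to specify one indicator. If pooling is not intended, the sentence misdescribes the model; if it is, the sentence does not fit the aim.

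**Exploratory status.** These analyses are preliminary, and the section itself concedes: "Although we will be unable to definitively explore these relationships in the proposed study". A direct comparison of the oils is promised only for the BDI, and a fish-oil-versus-placebo hypothesis does appear under Aims, for antidepressant use. All of this stands and limits the weight of the point. It does not explain why this one set of outcomes should have a different treatment term.

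**Stronger readings that the documents do not support.**

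- A reader might infer that the aim cannot be answered. It can: the randomised arm is held for every woman, and recoding the term requires no design change.
- A reader might take the fall from 80% to 37% as the expected loss. It holds only if exactly one oil acts, with an effect sized to give 80% power. The article gives no obstetric effect size.
- A reader might count empty preeclampsia cells against the plan. Taking the 5–8% general frequency in the Discussion as an assumed rate, with 42 per arm, the chance that at least one of three arms has no event is 1 − (1 − 0.95^42)³ = 31% at 5% and 1 − (1 − 0.92^42)³ = 9% at 8%. For 84 versus 42, the chance that either side has none is 13% and 3%. Sparse cells are thus mainly a cost of separating the arms, not a fault of a pooled term.

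**Conclusion.** The point holds at an exploratory level. As written, the obstetric models supply no separate EPA-rich and DHA-rich estimates, which is inconsistent with the third secondary aim and with the three-group models in the same section. This concerns a model term that the article states, not detail left to a fuller document.

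The size depends on what the oils do. Pooling halves the coefficient if one oil alone acts and gives zero if the effects are equal and opposite; it gains precision if the oils act alike. These figures rest on equal arms of 42 and a simple linear model. The conclusion also rests on reading the indicator as a single 0/1 variable, which is the plain reading but not the only possible one. The primary BDI analysis and the sample size are untouched.

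**What to change.** Replace the single indicator with a three-level arm term in the linear and logistic obstetric models. Report EPA-rich versus placebo and DHA-rich versus placebo, each with a 95% confidence interval. EPA-rich versus DHA-rich is an optional addition. Keep the pooled fish-oil contrast as a labelled supplementary line.

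If pooling is in fact intended as the main contrast, say so, give the reason, and align the wording of the third secondary aim.

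The change is one line in the model specification and needs no further data. The price is a standard error about 15% larger per contrast if the oils act alike, and thinner cells for rare outcomes such as preeclampsia, where an exact or penalised method may be needed.
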